### Ethical Considerations

Ethical approval of this trial was obtained from the institutional ethics committee (REF/2022/06/05559) of the Yenepoya (Deemed To Be University). Parent or guardians will be asked to provide a written informed consent form, which also covers the secondary analysis. All procedures will be conducted in accordance with the ethical standards of the Declaration of Helsinki and in accordance with relevant guidelines and regulations.

A participant information sheet describing the purpose of the study; details of the research, including the secondary analysis; procedures; and benefits and adverse effects, specifically tooth discoloration, will be given to the parents or legal guardians of the children. Their concerns about the adverse effects will be answered. Informed consent will be sought before the trial’s start. The study’s participants, including the children and their legal guardians, are free to discontinue at any moment during the study. Additionally, they are free to seek out extra dental treatment in accordance with their own preferences.

The drugs will be obtained by the primary investigator and are not sponsored. Drugs are stored at room temperature according to the manufacturer’s instructions. The manufacturer played no role in this study. The data safety sheet from the manufacturer for the SDF is provided in Multimedia Appendix 1. The drug controller general of India does not prohibit SDF use. Furthermore, no dental professional organizations or research associations have yet issued any SDF recommendations.

The privacy of the children will be respected. The data collected from the children will be kept confidential and will be shared only among the members of the research team, ethics committee, and regulatory authorities. No one else shall be privy to the children’s details. The photographs will be masked.

There will be a clinical evaluation for dental caries, during which the principal investigator will administer the necessary treatment if any pulpal involvement or abscess is found. The right to refuse or right to withdraw at any point of time will be given to the children. No monetary compensation will be provided in case of withdrawal. Participants who stay in the study will receive no monetary compensation, but will receive referral cards for further dental treatments at our institution free of cost.

### Risks and Discomforts

There are no major known risks to the study. There are minor risks, such as black stains on the carious tooth surface or temporary stains on the skin. Temporary stains on the skin will disappear within 48 hours without treatment. Participants who are allergic to the products will be excluded from the study.

## Results

Enrollment started in October 2023. It is estimated that the enrollment period will be 12 months. Data collection is planned to be completed in 2024.

## Discussion

### Principal Findings

Riva Star is a commercially available product that contains 38% SDF, so it will be used in the control group. Riva Star is the only commercially available product with 38% SDF+KI. As a result, it will be used in the case group. With oral administration, the average lethal dose (LD50) is 520 mg/kg. One drop (25 μL) contains 9.5 mg SDF, which is sufficient to treat 5 teeth. Considering that the smallest child with caries weighs around 10 kg, the dose would be 0.95 mg/kg. Hence, the relative safety margin for administering a complete drop to a 10-kg child is 380 mg/kg, so for an LD50 of 0.95 mg/kg the dosage is 400 times the safety margin. The actual dose is likely to be significantly lower. The recommended limit is 1 drop (25 μL) for 10 kg of body weight at every treatment visit. The maximum applied dose for 3 teeth is 2.37 mg, which would allow for over 400 applications [21].

Silver ions in the SDF solution have the potential to darken the tooth structure. It has been proposed that the KI solution can react with SDF to generate a bright yellow solid product (silver iodide), which could reduce the excess free silver ions that cause the black staining. Despite the presence of brilliant yellow precipitates following KI application, staining of tooth surfaces was still observed in an SDF+KI treatment group in a previous investigation. While KI is anticipated to eliminate SDF staining, its effect has not previously been quantified [22].

Patients are concerned about the aesthetic appearance of a restoration. Rather than analyzing color variations with the naked eye, which is typically subjective, we will quantify color changes using smart device measurements incorporating artificial intelligence, as these are more precise and repeatable [23].The Nix Mini color sensor is a wireless colorimeter that uses artificial intelligence to measure the exact color of surfaces and communicates the digital color values through Bluetooth to a smartphone or tablet. The color sensor blocks out ambient light and provides its own calibrated light source using the industry-standard 45/0° measurement. The device provides color readouts in International Commission on Illumination L*a*b* (CIELAB) format and calculates color differences in ∆E2000 [10]. The Nix Mini color sensor will be used immediately following treatment. From the Nix Mini color data, ∆L and ∆E values will be recorded and compared among the groups.

This is the first randomized controlled trial in which artificial intelligence–based sensing equipment and qualitative opinions of both the dentist (investigator) and parents will be ascertained. This study will help dentists and parents make the important clinical decision to choose a 2-step, noninvasive, low-cost treatment that is more acceptable and practicable in places lacking complete dental facilities, for hospital patients, and for low-income children with restricted access to comprehensive dental care.

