### Statistical Power

The sample size was calculated with G*Power (version 3; Universität Düsseldorf). Based on the results of Aly and Yousry [18], at a 5% level of significance and 95% power with an effect size of 1.594, (calculated by considering that the mean lightness value of one group was 71.3, SD 14.2 and the other group was 53.6, SD 6.7), and the primary end point being an evaluation of the staining propensity of SDF+KI at the end of 1, 3, and 6 months after treatment, with a 95% chance of detecting an increase in the mean lightness value from 53.6 in the control group to 71.3 in the experimental group, the minimum sample size in each group is 16. The expected dropout rate is 10%, so after considering the dropout rate, the sample size in each group is 30. Thus, the total sample required for the intervention will be 60 children (N=60).

For the secondary objective, with a significance level of 5%, a power of 80%, and an estimated critical *Z* value of 3.193, the study required 48 teeth, or 24 teeth per group. Finally, assuming 40% loss to follow-up, a sample size of 34 teeth was gathered in each group [19] to evaluate the caries-arresting effect of SDF+KI in the treatment of carious primary teeth at 6 and 12 months after treatment.

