#### Clinical Examinations

Clinical examinations will be performed by visual inspection under visible light, with the children in an upright position. The children will be assessed for dental caries using ICDAS codes and criteria. ICDAS codes 0-3 can be determined with air drying. Using a ball-ended World Health Organization (WHO) Community Periodontal Index probe, cavitated lesions (ICDAS codes 5 and 6) will be probed.

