#### Method of Application

In group 1, we will use cotton gauze to carefully clean and dry the affected tooth surface. The gingival tissue of the tooth will be protected with petroleum jelly. An applicator will be dipped into the SDF and 2-3 mg will be applied to the lesion with a microbrush, which will be used to paint the solution over the carious lesion; then, we will wait for 1 minute for absorption.

In group 2, we will apply SDF with the same technique. After the SDF application, KI will be applied using a separate microbrush, which will be saturated with the solution and will be used to paint the solution over the carious lesion. No rinse will be performed and special instructions will be given following application.

After treatment, an individual report on the child’s oral health will be provided, and after-treatment instructions will be given to the parents. If there is any adverse drug reaction associated with the SDF treatment, the parents will be asked to contact the principal investigator immediately by telephone.

All teeth will be photographed immediately after treatment. A high resolution mobile camera will be used to capture all of the images throughout the study. The high-resolution mobile camera features a 64-megapixel primary camera with an 8-megapixel secondary depth camera and an 8× optical zoom to provide images at a 2340×1080-pixel resolution.

Each tooth’s color will be measured using a Nix Mini color sensor. The Nix Mini color sensor is a wireless colorimeter that uses artificial intelligence to measure the exact color of surfaces and transmits the digital color values to a smartphone or tablet using Bluetooth.

Measurements will be calibrated in accordance with the manufacturer’s instructions to determine the first shade of the carious lesion. The ∆L and ∆E values will be measured 3 times by a single operator, and the average values will be noted. Despite the fact that SDF treatment had no adverse effects in other studies, if any adverse events occur, the primary investigator will duly report them to the institutional ethics committee.

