### Phase 3: Follow-Up

#### Primary Outcome Measures

Staining propensity will be measured 1, 3, and 6 months after treatment. Evaluation of the change in color of the carious lesions will use photographs and the Nix Mini color sensor.

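### The reference reading for the colour-change outcome (∆L, ∆E) has no stated pre-treatment time, and the only treatment-visit sensor timing given is after application

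*Protocol article*

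**What the plan says.** - **Outcome.** Primary Outcome Measures: "Staining propensity will be measured 1, 3, and 6 months after treatment". The same section defines the outcome as colour change in the lesions, assessed by photograph and Nix Mini sensor. The Abstract and Principal Findings name ∆L and ∆E as the recorded values, and Principal Findings says they will be compared between the groups.
- **Treatment visit.** Principal Findings: "The Nix Mini color sensor will be used immediately following treatment". Method of Application describes application in each arm, then parent instructions, then photographs ("All teeth will be photographed immediately after treatment"), then the sensor. Calibration of the sensor is said to serve "to determine the first shade of the carious lesion", with no time attached. It continues: "The ∆L and ∆E values will be measured 3 times by a single operator, and the average values will be noted". The reading that the ∆ is taken from is not named.
- **Baseline.** Phase 1 covers sociodemographic details and a clinical examination: "The children will be assessed for dental caries using ICDAS codes and criteria". Its text mentions no colour reading.
- **Sample size.** Statistical Power uses absolute lightness: "calculated by considering that the mean lightness value of one group was 71.3, SD 14.2 and the other group was 53.6, SD 6.7".
- **Analysis.** Data Analysis plans an unadjusted one-tailed t test or a Mann-Whitney U test.

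**The concern.** A ∆ is only as good as its reference. A reading taken after application is post-randomisation, so treatment can already have moved it. The article itself gives grounds to expect this, and to expect it unequally. The Introduction reports an immediate lessening of SDF staining once KI is applied, and Principal Findings describes a bright yellow precipitate after KI.

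If that reading is the reference, any between-arm difference already present is subtracted from ∆L. ∆E raises a further problem because it is an unsigned distance. If the precipitate fades later, the fading counts as colour change in the SDF+KI arm only, although it is not staining. The bias could therefore run in either direction. A pre-treatment colour that was never recorded cannot be recovered once the lesion is treated.

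**Working it through.** **1. The timing statements side by side**

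| Place | Reading | Time stated |
|---|---|---|
| Phase 1, Clinical Examinations | ICDAS; no colour reading in the text | before intervention |
| Method of Application | starting shade of the lesion | none |
| Method of Application | photographs | immediately after treatment |
| Principal Findings | Nix Mini sensor | immediately after treatment |
| Primary Outcome Measures, Table 1 | photographs and sensor | 1, 3 and 6 months |

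No row places a colour reading before application. The one row that might do so, the starting shade, has no time.

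**2. The planning figure**

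Inputs from Statistical Power: means 71.3 and 53.6, SDs 14.2 and 6.7.

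- Difference: 71.3 − 53.6 = 17.7.
- Common SD: √[(14.2² + 6.7²)/2] = √[(201.64 + 44.89)/2] = √123.265 = 11.10.
- Effect size: 17.7/11.10 = 1.594, as the plan states.

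This effect size is in absolute L*, not in ∆L.

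**3. What a post-treatment reference could do to ∆L (illustration only)**

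Let f be the share of the between-arm L* difference already present at the reference reading. The documents give no value, so f is assumed. The remaining contrast is 17.7 × (1 − f). Power is from the noncentral t distribution at the 5% level, with SD 11.10 and 27 per group (30 × 0.90).

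| f (assumed) | Units remaining | Power, two-sided | Power, one-sided |
|---|---|---|---|
| 0% | 17.7 | >99% | >99% |
| 25% | 13.3 | 99% | >99% |
| 50% | 8.9 | 82% | 89% |
| 75% | 4.4 | 30% | 42% |

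Two limits apply. The SD of 11.10 belongs to absolute L*. A change score has SD 11.10 × √[2(1 − r)], where r is the correlation of reference with follow-up. That equals 11.10 only at r = 0.5; at r = 0.3 it is 13.1. The table also covers ∆L only, since ∆E does not follow this formula.

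**4. What a pre-treatment reading adds to precision**

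Take s² as the variance of follow-up L*, with equal variance at both times and r assumed to be 0.3 to 0.5.

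- Variance adjusted for pre-treatment L*: (1 − r²)s² = 0.91s² to 0.75s², which is 9% to 25% below unadjusted follow-up L*.
- Adjusted variance relative to a raw change score: (1 − r²)/[2(1 − r)] = (1 + r)/2 = 0.65 to 0.75, which is 35% to 25% lower.

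This is a gain in precision, separate from the question of bias.

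**The case against.** A reader might infer that the trial does take its reference reading after treatment, so that ∆L and ∆E will be measured from an already treated lesion. The documents do not support this as fact:

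- Principal Findings says that the sensor is used after treatment. It does not call that reading the first, the only one that day, or the reference.
- The starting-shade phrase in Method of Application refers to the carious lesion, not the treated one, and may mean a pre-treatment shade.
- Paragraph order proves little. In that section, after-treatment advice to parents precedes the photographs taken immediately after treatment, so the text is arranged partly by topic.
- Figure 1 (the SPIRIT schedule, with a baseline time point) and Figure 3 are not shown and may list a baseline colour reading. Its absence from a condensed text is not itself an error.

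The size is also open. The value of f is assumed and may be zero, and the documents give no time course for SDF darkening. At f = 50% the illustrative one-sided power is still 89%.

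A reader might also infer that the primary comparison is lost. It is not. Absolute L* at follow-up needs no reference and is the quantity in the sample-size calculation. Randomisation balances initial colour in expectation, and covariate adjustment is often left to the analysis plan.

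All of this stands. What remains is that the one explicit timing, if followed for the reference, gives a ∆ affected by treatment, and that nothing in the text shown rules this out.

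**Conclusion.** The point holds as an ambiguity with a real consequence, not as a demonstrated flaw in the primary endpoint. The article makes colour change the primary outcome but does not say which reading it is measured from. Its only explicit treatment-visit sensor timing is one that would be unsuitable as a reference. Whether bias arises depends on two things the documents do not settle: whether the post-treatment reading is the reference, and how far the arms already differ at that moment. If both apply, the loss in ∆L could range from nothing to most of the planned 17.7 units, and the direction for ∆E cannot be predicted. Between-arm comparison of absolute follow-up L* remains valid in every case. The change is worth making because it is cheap and a missed reading cannot be replaced.

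**What to change.** 1. Reconcile Method of Application with Principal Findings: state that the triplicate Nix Mini reading and the photograph are taken on the cleaned, dried lesion before any application.
2. Define ∆L and ∆E at 1, 3 and 6 months against that reading. Keep the immediate post-treatment reading as descriptive.
3. Compare follow-up L* between groups adjusted for pre-treatment L*, in place of the unadjusted test.
4. For children already treated without a pre-treatment reading, compare absolute follow-up L*.

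If the schedule in the figures already includes a pre-treatment colour reading, step 1 is only a correction of wording.

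Cost: one extra reading of a few seconds per lesion at a visit already held, and revised analysis wording. Enrollment began in October 2023, so some enrolled children may lack a baseline value.

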**Methods:**

This study is a randomized controlled trial. A total of 60 children with caries that meet the criteria of the International Caries Detection and Assessment System (code 1 or above) will be randomly assigned to treatment groups, where group 1 will be treated with SDF and group 2 will be treated with SDF+KI. Discoloration of treated lesions will be assessed digitally using a Nix Mini color sensor. Participants will be followed up at 1, 3, and 6 months after treatment to digitally record the ∆L and ∆E values using the Nix Mini color sensor. Data will be analyzed using SPSS (version 28; IBM Corp). Independent sample *t* tests and the Mann-Whitney *U* test will be used to compare the 2 groups.

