In order to overcome this problem and increase the clinical use of SDF, a new method of application has been suggested [15]. This includes treating the initial layer of SDF with a layer of potassium iodide (KI), which combines with the free silver ions in SDF and inhibits the precipitation of silver phosphate. Since then, numerous investigations have shown that using KI after SDF creates a yellow silver iodide precipitate and prevents tooth stains from turning dark [10,16]. Following the application of KI in a dose-dependent manner, Detsomboonrat et al [17] noticed a considerable and immediate reduction in staining caused by SDF.

Studies demonstrating that KI reduces black staining are still insufficient. This paper presents the study protocol for Healthy Smiles, a randomized controlled trial implemented to compare the staining propensity of SDF+KI.

The aim of the study is to evaluate the staining propensity of SDF+KI among children aged 4 to 6 years by incorporating artificial intelligence in dentistry as a tool for precise interpretation of the findings, which will add to the evidence pool. The objectives of the study include (1) to evaluate the staining propensity of SDF+KI using a Nix Mini color sensor (Nix Sensor Ltd) among children aged 4 to 6 years, (2) to evaluate the caries-arresting effect of SDF+KI in the treatment of carious primary teeth, and (3) to assess parental satisfaction with dental appearance and color following treatment with SDF versus SDF+KI using a detailed questionnaire (Table 1). We hypothesized that there would be no difference in the staining propensity of SDF+KI among the children.

**Table 1 table1:** Objectives and measures.

Objectives	Measures	Description
1. To evaluate the staining propensity of SDF^a^ and SDF plus KI^b^ using the Nix Mini color sensor among children aged 4 to 6 years.	Child dental examination	At the end of 1, 3, and 6 months after treatment each tooth will be photographed and each tooth’s color change will be measured using the Nix Mini color sensor.
2. To evaluate the caries-arresting effect of SDF and SDF+KI in the treatment of carious primary teeth.	Arrest of carious lesions (6 and 12 months after treatment)	The progression in the size of the carious lesions will be evaluated using the ICDAS^c^ index as stable or progressing. The consistency of the lesions will be evaluated upon gentle probing using a ball-ended World Health Organization probe as soft or hard carious lesions.

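### ∆E2000 is compared between arms beside ∆L as a staining measure, but it has no direction, so a difference in ∆E cannot by itself be read as more or less staining

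*Protocol article*

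**What the plan says.** The Abstract (Methods) plans follow-up at 1, 3 and 6 months "to digitally record the ∆L and ∆E values using the Nix Mini color sensor". The Discussion (Principal Findings) adds "From the Nix Mini color data, ∆L and ∆E values will be recorded and compared among the groups" and says that the device "calculates color differences in ∆E2000". The primary outcome is given as "Staining propensity will be measured 1, 3, and 6 months after treatment" (Primary Outcome Measures), without a named colour coordinate or a direction.

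Three other places bear on how ∆E would behave:

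- The Introduction reports that "using KI after SDF creates a yellow silver iodide precipitate and prevents tooth stains from turning dark". The Discussion repeats the expectation of a yellow product. It applies only to the arm that receives KI.
- Statistical Power is set on lightness, as the chance of "detecting an increase in the mean lightness value from 53.6 in the control group to 71.3 in the experimental group". Higher lightness is the benefit.
- Method of Application says "The ∆L and ∆E values will be measured 3 times by a single operator, and the average values will be noted". It also mentions calibrating the measurements "to determine the first shade of the carious lesion", the nearest the article comes to naming a reference colour.

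**The concern.** The clinical question is black staining. ∆L has a sign: negative is darker, positive is lighter. ∆E2000 has none, since it is the length of the colour change in any direction. A lesion that blackens, one that lightens and one that turns yellow can all have the same ∆E. The article expects KI lesions to be lighter and to carry a yellow precipitate, so the experimental treatment may itself raise ∆E for reasons other than staining.

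If ∆E stands beside ∆L with no rule for reading it, the two comparisons can disagree and the report can lean on either. The one-tailed test in Data Analysis needs a favourable direction, and ∆E does not supply one. A smaller matter is the averaging of three ∆E values. Each is positive even when only measurement noise is present, so their mean is biased upward when the true change is small.

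**Working it through.** **Inputs from the article.** Mean lightness is 53.6 (SD 6.7) in the control arm and 71.3 (SD 14.2) with SDF+KI (Statistical Power). ∆E is ∆E2000 (Principal Findings).

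**Assumed, because the article does not give them.** Pre-treatment L* is varied from 55 to 70 and is common to both arms. Pre-treatment a* = 8 and b* = 25, unless stated otherwise. ∆ is taken from the pre-treatment shade.

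**The plan's own figure.** Pooled SD = √((14.2² + 6.7²)/2) = 11.10, and (71.3 − 53.6)/11.10 = 17.7/11.10 = 1.594. This reproduces the stated effect size and confirms that planning rests on lightness alone.

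**Signed ∆L.** For a common pre-treatment value L0, the arms differ by (71.3 − L0) − (53.6 − L0) = 17.7, whatever L0 is.

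**Unsigned ∆E2000.** With a* and b* unchanged the formula reduces to |∆L|/S_L, where S_L = 1 + 0.015(M − 50)²/√(20 + (M − 50)²) and M is the mean of the two L* values. At L0 = 60:

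- SDF: |∆L| = 6.4, M = 56.8, S_L = 1.085, ∆E = 5.9.
- SDF+KI: |∆L| = 11.3, M = 65.65, S_L = 1.226, ∆E = 9.2.

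A blackening lesion may also lose chroma, so the third column uses the full CIEDE2000 formula with SDF lesions moving to a* = 3, b* = 8 (assumed).

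| Pre-treatment L* | SDF, a*/b* fixed | SDF, chroma lost | SDF+KI, no yellowing |
|---|---|---|---|
| 55 | 1.3 | 10.2 | 13.7 |
| 60 | 5.9 | 11.7 | 9.2 |
| 62.45 (midpoint of 53.6 and 71.3) | 8.0 | 12.9 | 7.1 |
| 65 | 10.1 | 14.3 | 5.0 |
| 70 | 14.1 | 17.3 | 1.0 |

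The arms cross at about L* 62 with fixed chroma and about 58 with the chroma loss. Below the crossover the lighter arm has the larger ∆E.

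**Yellowing in the KI arm** (pre-treatment a* = 5, b* = 20, SDF chroma fixed). With b* +15, SDF v SDF+KI is 8.0 v 9.9 at L* 62.45 and 10.1 v 8.5 at L* 65, so the crossover lies between these. With b* +30 it is 10.1 v 13.0 at L* 65 and 14.1 v 12.0 at L* 70.

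**Spread within arms.** The figures above use arm means. As a simple stand-in for ∆E, |∆L| was simulated about a common baseline with the plan's SDs. Mean |∆L|, SDF v SDF+KI, is 7.6 v 14.8 at L* 60, 11.6 v 12.4 at 65 and 16.4 v 11.4 at 70. The wider SD in the KI arm lengthens an unsigned distance further.

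**Averaging three readings.** With an assumed reading SD of 2 per coordinate, the mean of three ∆E values compared with one ∆E from averaged L*a*b* is 2.4 v 1.4 at a true ∆E of 0, 4.8 v 4.4 at 4.2, and 13.9 v 13.7 at 13.7.

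**The case against.** The case for leaving the text alone has several parts.

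- **A directional measure is already planned.** ∆L is compared alongside ∆E and the sample size uses lightness, so a darker SDF arm would show. This stands. A reader might infer that interpretation of the whole primary endpoint hangs on unknown pre-treatment lightness; that is true of ∆E only.
- **No sentence says that a larger ∆E means more staining.** The outcome sections speak of colour change, which ∆E measures properly. This also stands as far as it goes. But the outcome is called staining propensity and the article itself commits to comparing ∆E between groups, so a reading rule is needed.
- **The ranking may be in a fuller document.** It may be. The ∆E comparison, however, is stated here without qualification.
- **The reversal rests on assumed colours.** Correct. A reader might infer from the lightness means alone that SDF+KI must look worse on ∆E below L* 62. The means do not establish that: plausible chroma loss under SDF lowers the crossover to about 58, while KI yellowing raises it.
- **The reference reading is unclear.** The first shade is mentioned among the post-treatment steps, and the Discussion has the sensor used just after treatment. If ∆ were taken from an immediate post-treatment reading, early lightening or yellowing would already be in the reference and the table would not apply.
- **The averaging bias is small.** It is, once there is a real change, and the article gives no sensor SD.

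**Conclusion.** The point holds as a should-fix. ∆E2000 is unsigned, the article expects non-black colour change in one arm, and nothing says whether ∆L or ∆E decides. A between-arm ∆E difference therefore cannot alone support a claim of more or less staining. On arm means, the comparison may be null or reversed when pre-treatment L* is below roughly 58 to 62, or at higher values if yellowing is marked. That range depends on the assumed a* and b* shifts and on ∆ being taken from the pre-treatment shade. With light lesions (L* about 70) and little yellowing, ∆E ranks the arms as intended. The documents do not show that reversal will occur, nor that the trial lacks a valid staining measure. Signed ∆L is such a measure and keeps its 17.7-unit difference at any common baseline. The averaging of ∆E is a minor addition.

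**What to change.** State in Primary Outcome Measures and Data Analysis that staining is judged on L* at follow-up or on signed ∆L, with negative meaning darker; this is the quantity behind the sample size. Name the reading from which ∆ is taken. Keep ∆E2000 as a descriptive measure of total colour change, report it with ∆a* and ∆b* so that yellowing is visible, and rest no claim of less staining on it. In Method of Application, as a minor change, record L*, a* and b* for each of the three readings, average those, and compute one ∆L and one ∆E from the averages.

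The device already reads out L*a*b*, so no visit, participant or equipment is added. The only loss is that ∆E can no longer carry a headline claim.
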